## Abstract

**Background:**

The traditional cross technique can be used to complete most laparoendoscopic single-site surgery (LESS) procedures, but some relatively precise operations, such as vaginal stump suturing, are challenging. In practice, we have introduced a novel technique named the chopstick technique and applied it to more complex operations, such as cervical cancer operations, and found that it contributes to performing delicate surgery. The efficacy and safety of two different surgical techniques in LESS hysterectomy remain to be validated.

**Methods:**

Patients who undergo total hysterectomy will be enrolled in this RCT. Stratified randomization will be performed according to uterine size (< 10 cm, 10–15cm, ≥ 15 cm). The participants will be divided into the chopstick technique group or cross technique group to undergo laparoendoscopic single-site total hysterectomy (LESS-TH), and then the perioperative and postoperative data, including the total operation time and other times, transfer rates, estimated blood loss, surgeon fatigue, intraoperative and postoperative complications (within 8 weeks after surgery), health-related quality of life (EQ-5D) scores, postoperative hospital stay, and hospitalization expenses, will be evaluated. The primary outcome is the operating time for total hysterectomy under LESS, and the other outcomes are secondary outcomes.

**Discussion:**

It is expected that the efficacy of the two techniques in LESS, the chopstick technique vs. the cross technique, will be compared and accumulate safety data on the new techniques will be accumulated.

**Trial registration:**

ChiCTR2000040843, registered on June 16,2020

Protocol version:

Version 2.0; Date: 2020.05.10

**Supplementary Information:**

The online version contains supplementary material available at 10.1186/s13063-022-06650-w.

## Background

Laparoendoscopic single-site surgery (LESS) is a favored alternative to traditional laparoscopy in minimally invasive surgery, with an esthetic advantage and can reduce postoperative pain from the incision as well as the use of analgesics [1, 2], which has been popular in cholecystectomy, nephrectomy, appendectomy, partial colectomy, and gynecological surgery [3–7].

All LESS operations are performed through a single puncture channel. Missing surgical triangles, instrument collisions, visual depth barriers, etc., are all problems that surgeons need to overcome. The “chopstick effect” is a dramatic description of the difficulties encountered in surgical operations with such close-range instrument layouts. To overcome the “chopstick effect,” surgeons have experimented with a variety of methods, of which front-bending instruments and the “cross technique” are widely used [8, 9]. Norihiko Ishikawa [10] specifically introduced the application of the “cross technique” for the first time in 2009; since then, the method has been mainstream. Boruta [11] used the “cross technique” to complete laparoendoscopic single-site radical hysterectomy in patients with cervical cancer. This surgical technique is shown in the LESS operation video, which is recommended by the American Association of Gynecologic Laparoscopists (AAGL): the surgeon is positioned on the left side of the patient, which is the same as in traditional laparoscopic surgery, the camera enters from the channel on the opposite side of the surgeon, and the surgical instruments enter from the channel on the same side as the surgeon. The left-hand instrument is mainly used for lifting and exposing, the right-hand instrument is mainly used for tissue separation and dissection, and the left-hand instrument makes a circular motion around the right-hand instrument. Because the core technique involves the crossing of two instruments around the umbilicus to complete the operation, this type of technique is called the “cross technique.” In clinical practice, we have explored another surgical technique that completely differs from the “cross technique” in terms of the position of the surgeon and the layout of the equipment. We named it the “chopstick technique” because it is similar to the manner in which Asians use chopsticks. We retrospectively analyzed 73 cervical cancer patients in which we applied the “chopstick technique” in LESS radical hysterectomy [12]. There were 72 successful cases that obtained the same clinical effectiveness as that of traditional multiple port laparoscopic surgery. The learning curve analysis among 44 cases of LESS cervical surgery showed that a significant reduction in operation time and complications could be achieved after performing 15 surgeries.

No comparative studies have been conducted to compare different surgical efficiencies between LESS techniques thus far. Therefore, this study intends to verify the value of the “chopstick technique” in LESS-TH by comparing surgical efficacy and surgeon fatigue.

## Methods

### Trial design

This single-center study will be a prospective, randomized controlled, double-blind, two-arm, parallel group, exploratory clinical trial carried out at the First Affiliated Hospital of the Third Military Medical University. The participant flow diagram is shown in Fig. 1.

**Fig. 1 Fig1:**
[figure not shown]
CONSORT flow diagram of the study. LESS, laparoendoscopic single-site injury

The protocol complies with SPIRIT standards (http://www.spirit-statement.org/), which are recorded in detail in the SPIRIT checklist.

### Participants

The inclusion criteria are as follows:Patients with indications for total hysterectomy, including uterine fibroids, adenomyosis, cervical precancerous lesions, endometrial atypical hyperplasia, IA1/LVSI-stage cervical cancer, early endometrial cancer (low-risk group), and Stage I endometrial stromal sarcomaPatients with American Society of Anesthesiology (ASA) scores of 1–3Patients aged 18–80 years

The exclusion criteria are as follows:Other malignant tumors or the need to expand the scope of surgeryA plan for intraoperative freezingPelvic organ prolapse, vulvovaginal disease, and appendiceal diseaseSuspected deep endometriosisA history of pelvic or abdominal radiotherapy, peritoneal dialysis, pancreatitis, or pelvic tuberculosisSurgical intolerance because of contraindicationsPoor complianceRefusal to provide informed consent

Patients will be stratified according to their uterine size without any exclusion regarding this aspect. The combination of salpingectomy or oophorectomy is also not an indication for exclusion since it makes no significant difference in the key operation steps and operation time.

### Interventions

Preoperative preparation

Patients will receive preoperative prophylactic antibiotics and will be given general anesthesia. A uterine manipulator will be placed.2.Surgeon

All the surgeons participating in the study are proficient in the two LESS techniques (“chopstick technique” and “cross technique”) and have completed more than 40 operations using both surgical methods [13], which cumulatively exceeds the learning curve turning point.3.Surgical treatmentThe position of the patient and the construction of a single-port channel

The patient is placed in the Trendelenburg position. A 2–2.5 cm longitudinal incision is made at the umbilicus layer-by-layer. The port incision protective sleeve is placed into the abdominal cavity and then tightened. The skin and the rectus abdominis are expanded and then connected with the port upper sealing cover, which forms a CO2 pneumoperitoneum.2)The surgeon’s position and instrument layout

Experimental group: the “chopstick technique” group [12]A.The position of the surgeons: The chief surgeon stands at the head of the patient, the camera assistant stands on the patient’s left, and the uterine-lift assistant stands between the patient’s legs.B.The layout of the instruments: The camera and the operator’s two-handed instruments are arranged into a triangle, the camera is located at the top corner of the triangle, and the two operating instruments are located at the bottom corners (Table 1).C.Operation technique: The surgeon’s hands are kept in a straight line with the instruments, and the operation skills are similar to those of traditional laparoscopy. The two instruments have independent fulcrums through the ports, which are not the fulcrums of each other.

**Table 1 Tab1:**
[figure not shown]
Characteristics and differences of the “cross” and “chopsticks” technique

Control group: the “cross technique” groupA.The positions of the surgeons: The chief surgeon stands on the patient’s left side, the camera assistant stands at the patient’s head, and the uterine-lift assistant stands between the patient’s legs.B.The layout of the instruments: The camera enters from the channel on the opposite side of the surgeon, and the operation channels are all on the same side of the surgeon.C.Operation technique: The left hand of the chief surgeon is mainly used for lifting and exposing, and the right hand is mainly used for tissue separation and cutting. The two instruments can cross each other through the ports to become each other's fulcrum, or the chief surgeon’s single-handed operation instrument and the assistant’s instrument form a cross fulcrum.3)Surgical steps

There are four steps to completed hysterectomy. Step 1: The periuterine peritoneum and superficial ligament are opened; the round ligament is cut off, the anterior broad ligament is opened, and the bladder and uterus reflexed peritoneum are separated. Step 2: The loose connective tissue around the uterus is separated, and the uterine arteries and veins are exposed and electrocoagulated. Step 3: A unipolar hook is used to remove the uterus along the fornix. Step 4: The vaginal stump is sutured with a barbed thread with a needle.4)Conversion of the surgical method

Regardless of whether a patient is in the “chopstick technique” group or “cross technique” group, when the operation is difficult, whether it will be converted to the other LESS technique/multichannel laparoscopy/laparotomy is decided through evaluation by 2 gynecologists.4.Postoperative care (under the enhanced recovery after surgery [ERAS] background)

Both groups will be nursed under the ERAS protocol [14]. Pain management will be standardized by the anesthesiologist. Patients will be encouraged to resume their diet and normal activities after surgery to facilitate functional recovery.

### Aims and objectives

Primary objective: the total operation time of the two LESS surgical techniques.

#### Secondary objectives

Single-port establishment time, pelvic-abdominal adhesion release time, total hysterectomy time (including salpingectomy or appendectomy time), specimen removal time, and vaginal stump suture timeSurgical conversion rate (switching to another LESS technique) and transfer rate (converting LESS surgery to traditional laparoscopy/laparotomy)Estimated intraoperative blood lossIntraoperative and postoperative complications (Clavien–Dindo grade≥ II级)Score for health-related quality of life (EQ-5D)Economic benefits with respect to hospitalization expensesPostoperative hospital staySurgeon fatigue

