**Assessments**								
Baseline characteristics			X					
Total operation time^a^				X				
Single-port establishment time^b^				X				X
Pelvic-abdominal adhesion release time^c^				X				X
Total hysterectomy time^d^				X				X
Specimen removal time^e^				X				X
Stump suture time^f^				X				X
Conversion to another LESS technique				X				X
Conversion to traditional laparoscopy /laparotomy				X				
Estimated blood loss^f^				X	X			X
Intraoperative complications				X	X			X
Surgeon fatigue (FSS)^h^					X			X
Post-operative hospital stay						X		X
Hospitalization expenses						X		X
Post-operative hospital stay						X		
Postoperative complications^i^							X	X
Health-related quality of life (EQ-5D)			X				X	X

^a^ Total operation time: the time from the beginning of the skin incision to the end of the operation

^b^ Single-port establishment time: the time from the beginning of the skin incision to the establishment of pneumoperitoneum

^c^ Pelvic-abdominal adhesion release time: the time taken to separate adhesions

^d^ Total hysterectomy time: the time from accessory/fallopian tube resection to uterine disconnection

^e^ Specimen removal time: the time taken to remove the uterus through vaginal or umbilical fragmentation

^f^ Stump suture time: the time taken for vaginal stump suturing with a single needle barb

^g^ Estimated blood loss: collected and evaluated by the intraoperative suction device

^h^ Fatigue Severity Scale (FSS): score on a 7-point scale (1 = strongly disagree, 7 = strongly agree), where a higher mean value manifests a higher degree of severity of fatigue symptoms [16]

^i^ Postoperative infection: lower abdominal pain with fever>38°C

We will not involve participant biological samples.

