### Main research indicators and the control of confounding factors and bias

The criteria of a newly successful technology are easy to master, preferred by surgeons and ultimately benefiting patients. However, these evaluation indicators are more complicated, with some being subjective, and some are difficult to evaluate. At present, the superior indicator for the evaluation of surgical techniques is operation time, which is also an objective evaluation parameter for differences in surgical techniques. The reduction in operation time can also indirectly reflect the benefits to patients. Therefore, this study selected operation time as the primary endpoint and other indicators, such as the fatigue of surgeons, as secondary indicators.

The size of the uterus affects the difficulty of total hysterectomy, which is the main confounding factor of the influence of the surgical technique on the operation time. According to the size of the uterus, we set up a stratified grouping study to eliminate the influence of uterine size as a confounding factor of the study. The intraoperative separation of adhesions is another influencing factor of surgical difficulty and a major research indicator in LESS hysterectomy. The study excluded cases that may cause severe intraoperative adhesions and added surgical time classifications during the operation: the single-port establishment time, pelvic-abdominal adhesion release time, total hysterectomy time, specimen removal time, and stump suture time, which eliminated research bias.

This study limits the qualifications of surgeons to those who have mastered both technical methods and have completed more than 40 LESS operations, thereby overcoming the learning curve of the new technology. Surgical videos of each operation are retained, and these will be evaluated by the clinical trial data monitoring committee (DMC). Above all, the research results will have better validity and universality.

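### The secondary outcome total hysterectomy time has no start event common to all patients and counts optional concomitant surgery inside the step

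*Protocol article*

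**What the plan says.** Four places in the protocol article bear on this outcome.

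- **Secondary objectives** define it by content: "total hysterectomy time (including salpingectomy or appendectomy time").
- **Table 2, footnote d** defines it by a clock: "Total hysterectomy time: the time from accessory/fallopian tube resection to uterine disconnection".
- **Participants** makes adnexal surgery optional: "The combination of salpingectomy or oophorectomy is also not an indication for exclusion". The reason given is "since it makes no significant difference in the key operation steps and operation time", with no figure. The same section lists appendiceal disease as an exclusion.
- **Interventions, surgical steps** begin the hysterectomy elsewhere: "Step 1: The periuterine peritoneum and superficial ligament are opened; the round ligament is cut off". None of the four steps is an adnexal or tubal resection.

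Table 2 footnote a defines the primary outcome, total operation time, separately: it runs from the first skin incision until surgery ends. The measurement section divides that total into five step times, of which hysterectomy time is one.

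**The concern.** A step time compares two techniques only if the clock starts and stops at the same events in every patient. Here the start is a procedure that some eligible patients may not have, and the interval contains that procedure in those who do.

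For a patient without adnexal or tubal resection, the person filling in the CRF must leave the time blank or choose a start. Blanks would restrict the comparison to patients with adnexal surgery; chosen starts would mix different intervals under one name.

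The two definitions can also disagree within a patient. A salpingectomy done after the uterus is disconnected counts under the Secondary objectives but falls outside footnote d. If the adnexa are resected after Step 1, or not at all, the Step 1 dissection belongs to none of the five components of the total.

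At stake is the interpretability of one named secondary outcome.

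**Working it through.** **The plan's own figure.** The documents state no figure for hysterectomy time. The sample size for the primary outcome reproduces and is not affected:

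- Difference: 170.1 − 125.72 = 44.38 min.
- Pooled SD: √((49.97² + 51²)/2) = 50.49 min.
- Two-sided t test at α = 0.05: power 0.898 with 28 per group and 0.908 with 29, so 29 per group as stated.
- Expansion by 15%: 29 × 1.15 = 33.35, rounded up to 34.

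**The definitions side by side, read literally.**

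| Patient | Start under footnote d | Adnexal work in the interval |
|---|---|---|
| Adnexal or tubal resection before the other dissection | Yes | Yes |
| Resection after Step 1 | Yes, but Step 1 is not timed | Yes |
| Resection after uterine disconnection | Start falls after the end | Outside the clock, yet counted by the Secondary objectives |
| No resection | None | None |

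The four rows measure four different things.

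**How many patients could lack a start.** The share p with adnexal surgery is not given. Assume p = 30–80%. The number per arm without a start is 34 × (1 − p): 34 × 0.2 = 6.8 to 34 × 0.7 = 23.8, or about 7 to 24 of 34. This holds only on the literal reading of resection.

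**How much noise the concomitant surgery adds.** The added time m is not given either. Assume m = 5–30 min.

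- SD of the chance difference in share between arms: √(2p(1 − p)/34) = 0.111 at p = 0.3, 0.121 at p = 0.5 and 0.097 at p = 0.8.
- SD of the resulting shift in the arm difference is that figure times m. Lowest: 0.097 × 5 = 0.5 min. At 20 min and p = 0.5: 0.121 × 20 = 2.4 min. Highest: 0.121 × 30 = 3.6 min.
- Added between-patient variance m²p(1 − p): from 25 × 0.16 = 4 min² to 900 × 0.25 = 225 min².

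**Comparison with the primary outcome.** The standard error for total time with 34 per arm is 50.49 × √(2/34) = 12.2 min. Even the largest shift, 3.6 min, is (3.6/12.2)² ≈ 9% of that variance. For hysterectomy time no SD is given, so the same ratio cannot be computed. Because that step is only part of the total, the relative share is probably larger.

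**The case against.** The strongest reply is that this is a wording matter in one of five secondary step times. Several parts of it stand.

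- **The literal reading may not be the intended one.** If resection means dividing the tube or adnexa from the uterus, every patient has a start event. The text does not say so, and an outcome definition should not need that guess.
- **Appendectomy and accessory are probably translation slips.** They fill the same slot beside salpingectomy and fallopian tube, and adnexal surgery fits both. A reader might infer a contradiction with the exclusion of appendiceal disease. That is weak: the exclusion concerns disease, not the procedure, and a slip is the likelier explanation. The terms still need reconciling.
- **A composite step can be legitimate.** Both definitions place adnexal work inside the step. A composite would be workable if it had a common start, which this one lacks.
- **Adnexal surgery is said not to matter.** The protocol's assertion that "it makes no significant difference in the key operation steps and operation time" has no figure behind it and supplies no start event.

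Two stronger inferences are tempting and should not be drawn.

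- A reader might infer that adnexal surgery biases the technique comparison, including the primary. If that surgery depends on age and indication, randomisation turns it into chance variation already carried in the standard error. Bias would arise only if the choice of extra resection depended on the allocated technique, and nothing in the document suggests this. Footnote a also fixes total time however footnote d is worded.
- A reader might infer that the step times defeat the purpose behind the Discussion's phrase "which eliminated research bias". That sentence follows from the problem of adhesions, and adhesion release has its own time. The wording is loose, but it does not carry this point.

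**Conclusion.** The point holds as a defect in the definition of one secondary outcome. The content definition, the clock, the eligibility rule and the surgical steps do not share one start event. On the literal wording, patients without adnexal or tubal resection cannot be timed, and in the others the step includes a procedure that differs from patient to patient.

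The consequence is poor comparability and added noise in hysterectomy time: a shift with an SD of about 0.5–3.6 min, on assumed shares of 30–80% and assumed durations of 5–30 min. Both ranges are assumptions. The definitional defect does not depend on them, but its practical size does. The primary outcome and the sample size are unaffected, and the point does not by itself call for a covariate in the primary analysis.

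**What to change.** 1. Start total hysterectomy time in every patient at the first action of Step 1 in the surgical steps, and end it at uterine disconnection. Use the same definition in the Secondary objectives and in footnote d.
2. Time concomitant adnexal procedures as a separate step, and take that time out of hysterectomy time.
3. Reconcile the Participants section, the Secondary objectives and footnote d on the terms appendectomy and accessory, stating whether adnexal surgery is meant.

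The cost is protocol and CRF wording and one more time stamp. One difficulty remains: where the adnexa come out in one piece with the uterus, adnexal time may not separate cleanly, so the CRF needs a stated convention for that case. Recruitment had already begun on July 1, 2021. The Monitoring section says a video of each operation is retained, for quality control review; those videos may allow the times to be recovered under the new definition for patients already treated.

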### Sample size calculation

The sample size was calculated on the basis of the primary outcome, namely, the total operation time. Current reports on the “cross technique” for LESS-TH show that the average operation time is 170.1 ± 49.97 min [15]. According to our pilot retrospective study of 46 patients undergoing LESS-TH with the “chopstick technique,” the average operation time was 125.72 ± 51 min. The difference between the average values of the two operation time was determined as the minimum difference. A bilateral difference test was used. The first-order risk (*α*) is 0.05, and the power (1-β) is set at 0.9 for the study. Based on the evaluation of PASS 25.0 statistical software, each group requires 29 patients. The study consists of equivalent numbers for each treatment arm. In consideration of the loss to follow-up and multiple surgeons’ influences on the operation time, the sample size was expanded by 15% to 34 patients for each group. A total of 68 patients are required for the experiment.

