## Limitations

This study will be a clinical study conducted at a single center, and the experience of doctors in the center may limit the universality of the conclusions of this study. RCT research will be conducted under ideal experimental conditions, and the surgeons are proficient in both surgical skills. It cannot be ignored that these two LESS technologies are used at different frequencies in a real environment, and the validity of the research results will be interpreted cautiously. Multicenter prospective cohort studies can increase the credibility of the results. However, this also increases the confounding factors of differences in surgeons’ operation skills.

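### Surgeon influence on operation time is answered by a shared 15% sample-size expansion, which can add precision but cannot remove a surgeon imbalance between arms

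*Protocol article*

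**What the plan says.** All references are to the protocol article.

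- **Sample size calculation.** The calculation gives 29 patients per arm. Citing loss to follow-up together with the effect of multiple surgeons, the plan then enlarges it: "influences on the operation time, the sample size was expanded by 15% to 34 patients for each group".
- **Randomization and blinding.** Uterine size, in three classes, is the only stratification factor. Allocation is by sealed envelope.
- **Statistical analysis.** Continuous outcomes are compared by a t test or a nonparametric test. BMI and age subgroups are foreseen. Surgeon is not mentioned.
- **Interventions (Surgeon).** All surgeons are to be proficient in both techniques and "have completed more than 40 operations using both surgical methods [13], which cumulatively exceeds the learning curve turning point".
- **Main research indicators and the control of confounding factors and bias.** Surgeons must have mastered both methods and "have completed more than 40 LESS operations, thereby overcoming the learning curve of the new technology".
- **Monitoring.** A video of each operation is kept so that the data monitoring committee can review technique and conversions.

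**The concern.** A larger sample and a balanced comparison are different remedies. More patients shrink random error. They do nothing about a systematic difference in who operates in each arm, or in how practised the surgeons are with each technique. The plan names surgeon influence as a threat to its primary outcome, but the design feature it attaches to that threat is the sample size. Neither the stratification nor the stated test involves surgeon.

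The safeguard that does address skill is the experience rule, and its count is not clear. The Interventions wording can be read as more than 40 operations with each technique, or more than 40 across the two. The later section counts LESS operations without dividing them by technique and refers to the learning curve of the new technology.

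If faster surgeons took a larger share of one arm, or surgeons were less practised in one technique, part of the measured difference would be credited to the technique.

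**Working it through.** **1. The plan's own figures.** Inputs from Sample size calculation: cross technique mean 170.1 min, SD 49.97; for the chopstick technique, "the average operation time was 125.72 ± 51 min"; two-sided alpha 0.05; power 0.90; equal arms.

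- Difference: 170.1 − 125.72 = 44.38 min.
- Pooled SD: √[(49.97² + 51²)/2] = 50.49 min.
- Noncentral t: power is 0.898 at 28 per arm and 0.908 at 29. The stated 29 is reproduced.
- Expansion: 29 × 1.15 = 33.35, rounded up to 34; 2 × 34 = 68. This is also reproduced.

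The arithmetic is sound. No surgeon variance enters it.

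**2. What the expansion can absorb as precision.** The largest variance inflation that still leaves an effective 29 per arm is 34 × (1 − loss)/29.

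| Loss | Patients left per arm | Design effect covered |
|---|---|---|
| 0% | 34.0 | 1.17 |
| 5% | 32.3 | 1.11 |
| 10% | 30.6 | 1.06 |
| 15% | 28.9 | 1.00 (none) |

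The article gives neither the number of surgeons nor their variance, so the next figures rest on assumptions. Let k surgeons share each arm equally, and let r be the share of total variance due to surgeon effects that differ by technique. The design effect is 1 + (34/k − 1)r. With no loss, 1.17 is reached at r = 0.172/(34/k − 1):

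- k = 2: 0.172/16 = 0.011
- k = 3: 0.172/10.33 = 0.017
- k = 4: 0.172/7.5 = 0.023
- k = 6: 0.172/4.67 = 0.037

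Even as a precision allowance it is modest.

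**3. What it cannot absorb.** With two surgeons, bias = (gap in operation time) × (difference in their case share between arms). Sample size does not appear in the formula. The assumed inputs are a gap of 20–40 min and a share difference of 20 points.

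- 20 × 0.20 = 4 min; 4/44.38 = 9%.
- 40 × 0.20 = 8 min; 8/44.38 = 18%.

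The standard error of the difference is 50.49 × √(2/34) = 12.2 min, so this bias is about 0.3 to 0.65 of a standard error. In simulation (20,000 trials, 34 per arm, no technique effect), a 20-point share difference raised the type I error of the unadjusted t test to about 0.06 for a 20-min gap and 0.08 for a 30-min gap.

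**4. Chance imbalance.** With two surgeons at 50% each, the SD of the share difference is √(0.25 × 2/34) = 0.12. Multiplied by 20–40 min, this is 2.4–4.8 min, against the 12.2-min standard error. When shares were equal in expectation, simulated type I error stayed at about 0.05. This is random error that the test already allows for.

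**5. The two experience rules.** Both require command of both techniques. Both use the figure 40. Interventions attaches it to operations using both methods; the later section attaches it to LESS operations. Neither says whether 40 applies to each technique or to the total.

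**The case against.** The case for the plan has real weight.

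- **Surgeon skill is not left to sample size alone.** A reader might infer that the 15% is the only safeguard. It is not: proficiency in both techniques and an experience count are required, and videos are reviewed. The rule limits learning-curve effects. It does not balance surgeons across arms, and the video review is quality control.
- **The two rules need not contradict each other.** If the count in Interventions is combined, the later wording is a shorter restatement. The word for cumulative there describes passing the learning-curve turning point and is not stated as the counting rule. What stands is an ambiguity.
- **Unequal expertise is not documented.** A reader might infer it from the Limitations remark that "these two LESS technologies are used at different frequencies in a real environment". That remark concerns practice outside the trial, and the same section calls the trial surgeons proficient in both. The chopstick technique is the centre's own, with a 46-patient pilot there, while the cross-technique figure comes from a cited report. This makes unequal practice conceivable, no more.
- **Randomisation protects against systematic imbalance** if each surgeon does both techniques and is assigned without regard to allocation. Reading chance imbalance as bias would be wrong.
- **A full protocol or analysis plan may set surgeon assignment and adjustment.** Silence on those details is therefore not held against the article. The point rests on what is stated: the purpose given for the expansion, the stratifier, the test and the two wordings.
- **The article does not say that the expansion removes confounding**, and enlarging a trial for extra variability is legitimate. Operation time is also recorded on the day of surgery, so later loss to follow-up should use up little of the allowance for this outcome.

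**Conclusion.** The point holds in a limited form. The trial acknowledges surgeon influence on its primary outcome and, beyond a proficiency and experience rule, meets it with an expansion that is at most a precision and attrition allowance. The stratification and the stated test do not take surgeon into account.

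The article does not support saying that surgeon does confound this comparison. Bias would need surgeon choice that depends on allocation, or unequal practice in the two techniques; the text neither shows nor excludes either. The 4–8 min shift depends wholly on the assumed gap and share difference, since the article gives no number of surgeons, no gap between them and no case shares. A shift of that size would be modest beside the planned difference, but it would matter more if the true technique effect were smaller than planned.

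**What to change.** 1. Name and record the operating surgeon for each patient before the envelope is opened. Recruitment has begun, so for patients already treated, record who operated and whether the assignment came before allocation.
2. Replace the unadjusted primary test with a linear model of operation time on technique, with surgeon and uterine-size stratum as fixed effects. With three strata and, say, two to six surgeons, this uses 2 + (1 to 5) = 3 to 7 of the 66 degrees of freedom.
3. Describe the 15% as an allowance for precision and attrition, not as control of the surgeon effect.
4. Reconcile the experience rule in Interventions with that in the section on confounding factors, so that it is clear whether the count is per technique or combined. Report each surgeon's prior count for each technique. This is needed because a surgeon term corrects unequal case shares but not unequal practice in the two techniques.

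The cost is one scheduling rule, a few model terms and some wording. No extra patients are required.
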